### Sample size determination

2.3

The primary outcomes of this study are PROs of functioning and well-being (WHODAS 2.0 and SWLS). We identified Hussain et al. (2025), who reported a between-group effect size of d = 0.8 on WHODAS 2.0 scores at the 20-week follow-up in a community-based, culturally adapted problem management intervention trial for people with disability (35). We use this study to inform our sample size calculation since the follow-up duration and outcome measure closely align with our six-month endpoint. Although Hussain et al. (2025) used the 12-item WHODAS 2.0 version, psychometric studies have demonstrated high concordance between the 12- and 36-item versions (correlation coefficients of *r* ≥ 0.915 between total scores on these two versions). This strong agreement supports the application of an effect size derived from the 12-item version to the 36-item WHODAS 2.0.

Using G*Power (G*Power 3, version 3.1.9.6) (36), with a α level of 0.05 (two-tailed), a power of 0.80, and an effect size of 0.8 as reported, a minimum sample size of approximately 26 participants per group (a total of 52 participants) was determined. Assuming a 15% attrition rate (18), the study will recruit a total of 60 participants who are PWD, newly referred and eligible service users of home care services. Considering that approximately 120–160 new case referrals are received per year, recruitment will take a minimum of 6 months.

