## Data analysis

3

Data analysis will begin only after the follow-up stage. The PI and SI will have access to the final trial dataset. The quantitative data will be analysed via SPSS Statistics 27.0 (IBM). Data cleaning will include systematic screening for outliers and any inconsistencies in the data. Multiple imputations will be considered for missing data. Descriptive statistics will be applied as appropriate for all variables.

**Primary outcomes.** To determine whether functioning (WHODAS 2.0) and subjective well-being (SWLS) improve following the implementation of the ICFIDCM, we will compare intervention and control groups via generalised linear mixed models (GLMMs). Fixed effects will include time (baseline, 6 months), study group, and the group × time interaction, with participant ID as a random effect to account for repeated measures. The target test statistic will be the mean difference (with 95% confidence intervals), estimated via maximum likelihood methods. Two-sided significance will be set at 0.05. **Secondary outcomes.** To analyse the target secondary outcomes (ICF qualifiers and AusTOMs) over the course of time, descriptive analyses will first summarise change scores over time. Subsequently, GLMMs will be used to estimate group differences in changes, with the same fixed- and random-effects structure as above. The results will be expressed as estimated marginal means with 95% confidence intervals.

Treatment dosage variables (e.g., number of visits, total contact time) will be recorded and included as covariates in exploratory sensitivity analyses to assess their potential influence on treatment effects. Although the study is not powered for formal subgroup comparisons, exploratory sensitivity analyses will be performed to examine potential effect modification. Specifically, interaction terms between group allocation and age group, primary diagnosis, and treatment dosage will be examined within the mixed-effects model framework. These analyses are exploratory in nature and will be interpreted cautiously given the limited sample size.

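### Estimating the primary contrast by full maximum likelihood with 51 to 60 participants makes its tests and intervals slightly anti-conservative; name REML and a degrees-of-freedom method

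*Protocol article*

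**What the plan says.** The Data analysis section (section 3) gives WHODAS 2.0 and SWLS the same model. On the structure it says: "Fixed effects will include time (baseline, 6 months), study group, and the group × time interaction, with participant ID as a random effect". On estimation it says: "The target test statistic will be the mean difference (with 95% confidence intervals), estimated via maximum likelihood methods". On the significance level it says: "Two-sided significance will be set at 0.05". It does not say whether maximum likelihood is full or restricted. It also gives no distribution or link, no reference distribution and no degrees of freedom for the test.

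For the secondary outcomes, the same section says: "Subsequently, GLMMs will be used to estimate group differences in changes, with the same fixed- and random-effects structure as above". That sentence carries over the model structure and does not mention the estimator.

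Section 2.3 sets the size of the trial: "a minimum sample size of approximately 26 participants per group (a total of 52 participants) was determined". It then allows for 15% attrition and recruits 60. Section 2.9 fixes two assessments, at baseline and at six months.

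**The concern.** For a mixed model, maximum likelihood ordinarily means full ML, and restricted ML is usually named when it is intended. Full ML makes no allowance for the fixed effects when it estimates variances. In a large trial this is invisible. With 51 to 60 participants it is small but measurable, and it always acts in the same direction: standard errors too small, intervals too narrow and p-values too low. The sentence governs both primary outcomes. An estimator without this bias is available at almost no cost, so the choice is worth correcting before the analysis begins.

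**Working it through.** **Inputs from the protocol article**

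- Section 2.3: two-sided α 0.05, power 0.80, d = 0.8; 26 per group, 52 in total; 15% attrition; 60 recruited.
- Section 2.9: two visits.
- Section 3: fixed effects of time, group and group × time; participant as random effect; two-sided 0.05.

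**Assumption not in the article:** a normal model with identity link. The stated target, a mean difference, fits this.

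**Step 1: the planned size.** A two-sample t test with d = 0.8 and two-sided α = 0.05 has power 0.791 with 25 per group and 0.807 with 26 per group, so the stated 26 is reproduced. With 15% attrition, 60 × 0.85 = 51 participants have follow-up data. The relevant range is therefore N = 51 to 60.

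**Step 2: the standard error.** With two visits, complete data and a random participant intercept, the group × time estimate is the between-group difference in mean change. ML divides the residual sum of squares of the changes by N; the unbiased (REML) estimate divides it by N − 2. Hence

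SE(ML) / SE(REML) = √((N − 2)/N)

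- N = 60: √(58/60) = 0.983, so the SE is 1.7% too small.
- N = 51: √(49/51) = 0.980, so the SE is 2.0% too small.

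**Step 3: the actual type I error.** The ratio of the estimate to its REML standard error follows t on N − 2 degrees of freedom (df) under the null. If the ML ratio is compared with a critical value c, then

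actual α = 2 × P(t on N − 2 df > c × √((N − 2)/N))

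Example for N = 60 with the normal value c = 1.960: 1.960 × 0.983 = 1.927, and 2 × P(t on 58 df > 1.927) = 0.0589.

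| Reference for the test | ML, N = 60 | ML, N = 51 | REML, N = 60 | REML, N = 51 |
|---|---|---|---|---|
| t on N − 2 df | 0.0538 | 0.0545 | 0.0500 | 0.0500 |
| t on 2N − 4 (residual) df | 0.0563 | 0.0575 | 0.0524 | 0.0528 |
| Normal | 0.0589 | 0.0605 | 0.0548 | 0.0557 |

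A likelihood-ratio test under ML gives 0.0550 at N = 60 and 0.0559 at N = 51.

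**Step 4: separating the two sources.** The first row isolates the estimator, which adds 0.4 to 0.5 percentage points. The REML columns isolate the reference distribution: a normal reference alone adds 0.5 to 0.6 points. Only together do they reach 0.059 to 0.061, so about half of the worst-case excess is not due to ML.

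**Step 5: coverage.** Coverage is one minus the actual α. It runs from 1 − 0.0605 = 0.9395 to 1 − 0.0538 = 0.9462, that is, about 93.9% to 94.6%.

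**Step 6: missing follow-up.** A simulation used 60 randomised participants, 9 follow-ups missing at random, an assumed within-person correlation of 0.5, no true effect and 1,500 runs. The mean SE ratio ML/REML was 0.981, in line with Step 2. The two point estimates never differed by more than 0.0005 SD. With a normal reference, rejection rates were 0.059 under ML and 0.054 under REML; with t on 49 df they were 0.052 and 0.046. Monte Carlo error is about 0.006, so the simulation confirms the SE ratio but does not pin down the type I error more closely than the exact formula.

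**The case against.** The strongest objection is that the phrase is generic. It is in the plural, it never excludes the restricted form, and a journal article commonly leaves REML against ML, and the df method, to the analysis plan. This stands in part: the anti-conservatism is conditional on full ML being meant. It does not remove the point, because the article does name an estimation method, and on its ordinary reading that method is the less suitable one at this size. If REML was meant, adding that word settles the matter. The absence of a df method is not itself counted against the article; it matters here only because the size of the error depends on it.

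A second objection is that the effect is small and partly due to something other than ML. This stands in full. The SE is off by about 2%, the estimate does not move, and about half of the largest excess comes from an assumed normal reference.

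Two stronger readings are tempting, and the article supports neither. A reader might infer that the primary tests and intervals are invalid; an actual α of 0.054 to 0.061 and coverage near 94% do not justify that. A reader might also infer that every secondary outcome is affected. The secondary-outcome sentence carries over only the fixed and random effects, and the ICF qualifiers are ordinal codes for which no distribution or link is given, so the formula above need not apply to them.

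**Conclusion.** The point holds, and it is minor. Read as full ML, the stated estimator makes the SE of the primary group × time contrast 1.7% to 2.0% too small. Actual two-sided α is 0.054 to 0.055 from ML alone and at most 0.059 to 0.061 with a normal reference. Only a p-value close to 0.05 could change sides.

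The conclusion rests on three assumptions: that full rather than restricted ML is meant, that the model is normal with identity link, and that N is 51 to 60 as planned. The formula is exact for complete two-visit data, and the simulation shows essentially the same SE ratio with 15% of follow-ups missing. The conclusion is confined to the primary outcomes and to any secondary outcome that is analysed with a normal model.

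**What to change.** In section 3, under the primary outcomes, replace the reference to maximum likelihood methods with: *linear mixed model (normal, identity link) fitted by restricted maximum likelihood, with Satterthwaite or Kenward-Roger degrees of freedom for the between-group contrast and its 95% confidence interval*. Use the same wording for any secondary outcome analysed with a normal model. If REML was already intended, naming it and the df method is enough.

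The cost is one sentence, with no change to data collection or sample size. Compared with ML and t on N − 2 df, intervals widen by 1/0.983 − 1 = 1.7% (N = 60) to 1/0.980 − 1 = 2.0% (N = 51). Compared with ML and a normal reference, they widen by 2.002/(1.960 × 0.983) − 1 = 3.9% to 2.010/(1.960 × 0.980) − 1 = 4.6%. The article says that analysis starts only after follow-up, which is expected to end by 31 July 2026, so on that timetable the wording can be settled before analysis begins.

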### Research aim

2.1

The trial aims to evaluate the effectiveness of the ICFIDCM compared with that of usual multidisciplinary care in improving the functioning and well-being of people with disabilities who receive home-based community rehabilitation. Two primary outcome indicators, which are both patient-reported outcomes (PROs), are functioning (World Health Organization Disability Assessment Schedule 2.0, WHODAS 2.0, 36-item version) and well-being (Satisfaction with Life Scale, SWLS). Two secondary outcome indicators, therapist-reported outcomes (TROs), are changes in ICF qualifiers and Australian Therapy Outcome Measures (AusTOMs). We hypothesised that, compared with the usual care control group, participants receiving the ICFIDCM would demonstrate greater improvements from baseline to six months in terms of functioning (lower WHODAS 2.0 scores) and subjective well-being (higher SWLS scores). For the secondary outcome, compared with the control group, we expect to see greater pre-post improvements in therapist-rated functioning (improved ICF qualifier scores) and in therapist-rated clinical outcomes (higher AusTOMs scores) among participants in the intervention group.

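### Two unranked primary outcomes share one 0.05 level with no testing rule, and the 80% power covers WHODAS 2.0 only

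*Protocol article*

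**What the plan says.** Section 2.1 (Research aim) introduces "Two primary outcome indicators, which are both patient-reported outcomes (PROs"), namely WHODAS 2.0 and SWLS. Its hypothesis covers both: "greater improvements from baseline to six months in terms of functioning (lower WHODAS 2.0 scores) and subjective well-being (higher SWLS scores"). Neither outcome is placed ahead of the other, and Section 2.3 again calls both primary.

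Section 2.3 (Sample size determination) takes its effect size from one earlier trial, which "reported a between-group effect size of d = 0.8 on WHODAS 2.0 scores at the 20-week follow-up". The calculation is run "with a α level of 0.05 (two-tailed), a power of 0.80, and an effect size of 0.8 as reported", and "a minimum sample size of approximately 26 participants per group (a total of 52 participants) was determined". No effect size or power is given for SWLS.

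Section 3 (Data analysis) treats the two outcomes in one paragraph with the same mixed model for each. The only statement there about the error rate is "Two-sided significance will be set at 0.05".

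**The concern.** With two primary outcomes, a trial needs a rule that says what counts as a positive result. The article fixes the number of primary outcomes, the significance level and a sample size that spends the whole 0.05 on one of them, but it does not fix that rule.

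Two things follow. If a significant result on either outcome can be presented as a primary finding, the chance of at least one false positive exceeds 5%. And that finding could be SWLS alone, for which the trial was not sized. If instead both outcomes are needed, the error rate is controlled, but the 0.80 in Section 2.3 does not describe the chance of reaching the claim in Section 2.1. The Discussion links a positive result to scale-up, service planning and policy, so the reading should be settled before anyone sees results.

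**Working it through.** **Inputs from the article.** Two primary outcomes (2.1, 2.3); two-sided level 0.05 (2.3, 3); power 0.80 and d = 0.8 on WHODAS 2.0 (2.3); 26 per group, 60 recruited, 15% attrition (2.3).

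**Assumptions, because the article gives no figures.** The correlation r between the two test statistics is varied from 0 to 0.9. Power on SWLS is set at 80% where a joint figure is needed.

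**1. The article's own sample size.** A two-sample t-test (noncentral t) with d = 0.8, two-sided alpha 0.05 and power 0.80 gives n = 25.52, so 26 per group. Power at 26 per group is 0.807. The stated figure reproduces for one WHODAS 2.0 test at the full 0.05. After 15% loss, 60 × 0.85 = 51 remain, about 25.5 per group, and power is 0.800. There is no reserve.

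**2. Either outcome sufficient, each tested at 0.05.** If the tests are independent, familywise error = 1 − (1 − 0.05)² = 1 − 0.9025 = 0.0975. For correlated tests, error = 1 − P(|Z1| < 1.96 and |Z2| < 1.96), with Z1 and Z2 bivariate normal with correlation r:

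| r | familywise error |
|---|---|
| 0 | 9.75% |
| 0.5 | 9.1% |
| 0.7 | 8.3% |
| 0.9 | 7.0% |

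**3. Both outcomes required.** Error is at most 5%. With 80% power on each, joint power = P(Z1 < 0.842 and Z2 < 0.842), where 0.842 is the 80th percentile of the standard normal:

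| r | joint power |
|---|---|
| 0 | 0.8 × 0.8 = 0.64 |
| 0.5 | 0.69 |
| 0.7 | 0.71 |
| 0.9 | 0.75 |

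The 80% for SWLS is only an assumption. If the true SWLS effect were d = 0.5, the same t-test at 26 per group and 0.05 would have power 0.42, and joint power could be no higher than that.

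**4. Alpha split equally.** At 0.025 each, the t-test used in Section 2.3 has power 0.716 for d = 0.8 at 26 per group. It would need 31 per group (n = 30.99) for 80%.

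**5. Fixed sequence, WHODAS 2.0 first.** WHODAS 2.0 is tested at 0.05 with power 0.807, as in step 1. SWLS is tested at 0.05 only after a significant WHODAS 2.0 result, so familywise error stays at or below 5%. This needs no change to the sample size.

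**The case against.** The strongest reply is that the stated power is not wrong. Section 2.3 ties 0.80 to a WHODAS 2.0 effect at 0.05, and 26 per group delivers it. No joint power is claimed, so the joint figures in step 3 contradict nothing in the article. This stands. A reader might infer that either the 5% error rate or the stated 80% power must fail. The documents do not support that, because the sequence in step 5 keeps both with the present sample size.

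Second, Sections 2.1 and 3 join the outcomes with a plain conjunction, which could mean that both are required. Then the error rate is not inflated and SWLS alone could not make the trial positive. This is a possible reading, so the inflation in step 2 is conditional. But a conjunction in a hypothesis is not a decision rule, and the article never says that a result on one outcome alone would not count.

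Third, the article gives 0.05 once and does not say that it applies to each outcome separately, and an analysis plan that is not shown may contain the rule. Testing each at 0.05 is the natural reading, but it is an inference. Even so, the article itself fixes two equal primary outcomes and a sample size that spends all of the 0.05 on one of them. An equal split of alpha elsewhere would lower the power that Section 2.3 states, and a sequence would add a ranking that the article does not contain.

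Fourth, the 0.716 in step 4 belongs to a comparison of follow-up scores, while Section 3 plans a mixed model with a group-by-time term. Under that model, power depends on the correlation between baseline and follow-up, which is not given. Step 4 is therefore illustrative, and the conclusion does not rest on it.

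**Conclusion.** The concern holds in a limited form. The article names two primary outcomes of equal rank and sets one 0.05 level for both, without a testing order, alpha split or success rule. If either outcome may support a primary claim, familywise error is 7.0% to 9.75% for correlations from 0.9 down to 0. The 80% power is right for WHODAS 2.0 and should be read as applying to that outcome alone. If both outcomes were required, the chance of success would be about 0.64 to 0.75 over the same range of correlations, provided SWLS also had 80% power, which the article does not show.

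This is a should-fix. The sample size arithmetic is sound, and what is needed is one explicit rule, set before the data are analysed.

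**What to change.** In Section 3, state that WHODAS 2.0 is tested first at two-sided 0.05 and that SWLS is tested at two-sided 0.05 only if WHODAS 2.0 is significant. Otherwise SWLS is reported as an estimate with its 95% confidence interval and no confirmatory claim. In Section 2.3, state that the 80% power applies to WHODAS 2.0 only.

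The cost is two sentences, with no extra participants and no loss of power for WHODAS 2.0. The downside is that SWLS cannot yield a confirmatory claim if WHODAS 2.0 fails, which places it below an outcome to which Section 2.1 gives equal standing. Requiring both outcomes would also control the error rate, but Section 2.3 would then have to give an SWLS assumption and the joint power. Section 3 starts analysis only after follow-up, which Section 5.2 expects to end by 31 July 2026, so the rule can be recorded before then.

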Following the baseline assessment, participants will be randomly assigned at a 1:1 ratio to either the intervention group or the control group, as stated before. This study is single-blinded: participants will not be informed of their group allocation, whereas the case managers and allied health professionals responsible for assessment and intervention delivery will be aware of the group assignments owing to the nature of the assessment/intervention.

The intervention group will receive structured ICFIDCM, which includes collaborative goal setting, monthly interdisciplinary case conferences, and coordinated care planning on the basis of ICF assessments. The control group will continue to receive usual multidisciplinary care involving standard discipline-specific assessments and interventions without structured interdisciplinary case management. During the six-month period, participants are permitted to continue all routine medical services and medications that participants are already receiving at baseline. The case managers will contact the case regularly via phone for check-in or service arrangements. If a participant is admitted to the hospital for new medical treatment or if their condition changes significantly, the case manager will notify the SI. Such events and any subsequent change in the intervention or usual care delivery will be recorded as protocol deviations.

All outcome assessments will be repeated at six months post-intervention. Throughout the study, participants' data and outcomes will be securely stored on an encrypted, password-protected server. Only authorised study personnel will have access, and data will be anonymised using the unique case referral number as the study code. Personal identifiers in documents are stored in locked filing cabinets to maintain confidentiality (Figure 1).

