### Intervention

2.8

Both intervention and control groups are served by the same interdisciplinary team of social workers, physiotherapists, occupational therapists, speech therapist, and nurses. Professional contacts will be individualised based on participants' clinical and functional needs, with frequency, duration, and intensity determined by routine service criteria. Since both groups are delivered in the same service setting and resource structure, protocol-driven differences in treatment intensity or overall service provision are not anticipated. All professional contacts will be systematically recorded. The primary distinction between groups lies in the care coordination structure, as detailed in Sections 2.8.1, 2.8.2.

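### Exploratory dosage analysis: as written it cannot move the group × time estimate, and the forms that can move it are confounded by need (minor)

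*Protocol article*

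**What the plan says.** Section 3 (Data analysis) gives the primary model: fixed effects for time at two levels, "study group, and the group × time interaction, with participant ID as a random effect". The target is a mean difference. Section 2.1 states the hypothesis as greater improvement from baseline to six months, so group × time carries the treatment effect.

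Dosage enters in two ways. Visit counts and overall contact time are "included as covariates in exploratory sensitivity analyses to assess their potential influence on treatment effects". In addition, "interaction terms between group allocation and age group, primary diagnosis, and treatment dosage will be examined within the mixed-effects model framework". No dosage × time or group × time × modifier term is named. The analyses are called exploratory, and the reason given for caution is the small sample.

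On how dose arises, section 2.7 says: "Following the baseline assessment, participants will be randomly assigned at a 1:1 ratio". The contacts of the study period therefore accrue after allocation. Section 2.8 ties them to participants' "clinical and functional needs, with frequency, duration, and intensity determined by routine service criteria", expects no protocol-driven difference in intensity between arms, and adds: "All professional contacts will be systematically recorded". Section 2.4 keeps withdrawn cases in the analysis with their latest available data.

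**The concern.** A different amount of professional contact is an obvious rival explanation for any benefit. Section 2.8 rules it out by expectation and places the main distinction between arms in care coordination. The dosage analysis is the named check on whether contact influences the treatment effect.

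A variable with one value per participant cannot explain a within-participant change unless it is allowed to act on change. If the analysis is run as worded, a report that the effect was unchanged after adjustment for dosage would be true by construction, yet readers would take it as evidence. If dosage is instead allowed to act on change, the adjusted comparison conditions on something that happened after randomisation and follows need. A larger sample would not remove that problem, and it is not the caution that the section gives.

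**Working it through.** **Plan's own figures.** The plan gives none for the dosage analysis. The sample size used in step 5 reproduces: a two-sample t-test with d = 0.8, two-sided alpha 0.05 and power 0.80 gives 25.52, so 26 per group (power 0.807); 60 are to be recruited.

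**1. Algebra of the literal reading.** With g = group, t = 0 or 1, D = dosage total and u = participant effect:

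y(t) = b0 + b1·g + b2·t + b3·g·t + c·D + d·g·D + u + e(t)

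y(1) − y(0) = b2 + b3·g + e(1) − e(0)

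Both dosage terms drop out. With both visits present for everyone and an identity link, the estimate of b3 is the between-arm difference in mean change, with or without D.

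**2. Simulation of that result.** 400 trials of 60, random-intercept model by maximum likelihood. Assumed: y0 ~ N(0,1); dose = 1.0·g + N(0,1); y1 = 0.7·y0 − 0.8·dose + 0.5·N(0,1). Dose thus carries the whole 0.8 SD effect. Mean group × time:

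| Model | Complete | 9 of 60 carried forward | 9 of 60 missing |
|---|---|---|---|
| No dosage | −0.776 | −0.682 | −0.795 |
| + total dosage | −0.776 | −0.682 | −0.794 |
| + total and group × dosage | −0.776 | −0.682 | −0.795 |
| + dosage coded by visit (0 at baseline) | 0.008 | −0.008 | 0.006 |
| + dosage × time | 0.011 | −0.007 | 0.005 |

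The largest change from adding a total was 6e-15 with complete data and 5e-15 with carried-forward data. With 9 of 60 missing (15%) the mean absolute change was 0.016 and the largest 0.08.

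**3. Dosage allowed to act on change.** The change model becomes b2 + b3·g + c·D. Least squares gives adjusted b3 − unadjusted b3 = −c × (between-arm dose difference), so with no dose difference nothing moves. If dose is inert but correlates r with need, and need affects change by k, then c = r·k. Assumed values, true direct effect −0.8 SD, shift from adding dosage × time:

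| Dose difference (SD) | r = 0.5, k = 0.3 | r = 0.7, k = 0.5 |
|---|---|---|
| 0 | +0.001 | −0.003 |
| +0.25 | −0.040 | −0.090 |
| +0.5 | −0.074 | −0.179 |
| +1 | −0.153 | −0.354 |
| −0.5 | +0.078 | +0.175 |
| −1 | +0.147 | +0.348 |

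For example, −1 × 0.7 × 0.5 = −0.35 against −0.354 simulated. A separate simulation on a points scale (true effect −8, inert dose, 200 trials per setting) agrees. With arms six visits apart, −8.29 stayed −8.29 with a total covariate but became −13.25 (coded by visit) or −12.10 (crossed with time). With equal dose, −8.05 became −7.96 under both.

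**4. Age group and diagnosis.** Randomisation makes the expected group difference at baseline zero in every modifier level. A group × modifier term without time therefore averages 0 and the six-month modification δ, giving δ/2. For δ = −0.40 SD the expected two-way term is (0 − 0.40)/2 = −0.20 (simulated −0.171, simulation error 0.027). The three-way term gave −0.400 with SE 0.38 to 0.42, so a half-width of 1.96 × 0.38 = 0.74 to 1.96 × 0.42 = 0.82 SD.

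**5. Precision of a direct dose comparison.** The half-width is t(0.975, 2n − 2) × √(2/n), which is 0.517 SD at n = 30 per arm and 0.557 SD at n = 26.

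**The case against.** The strongest reply is that a condensed article need not give the coding of an exploratory covariate, and that interactions with group allocation may be shorthand for modification of the group × time effect, that is, three-way terms. The second part stands as a possibility, so the halving in step 4 applies only to the literal wording. For dosage the reply goes less far. The article states a rule and its purpose, and choosing a different coding does not meet that purpose without a further assumption about need.

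A reader might infer from step 2 that the two codings give opposite answers. The documents do not support that as a general statement. It holds there because a 1 SD dose difference and full mediation were assumed. Section 2.8 expects no protocol-driven difference, and at zero difference the codings agree.

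The mean difference could also be read as the six-month difference, which a total does move: in one simulated trial from −4.75 to −10.95. Group × time stayed at −4.45, so the baseline difference moved from −0.30 to −6.50, the same shift of about −6.2. This is no information about change, which section 2.1 makes the hypothesis.

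Finally, the analyses are labelled exploratory, to be read with caution, and "Descriptive statistics will be applied as appropriate for all variables", which may already tabulate dose by arm. All of this stands and limits the severity. What remains is that no between-arm dose estimate with an interval is named, and that the caution concerns only sample size.

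**Conclusion.** The point holds at minor severity and concerns the exploratory analyses only. Read literally, the dosage covariate and group × dosage cannot change the group × time estimate. This is algebraic. It needs an identity link (supported by the mean-difference target), change from baseline as the effect, and complete or carried-forward data; with about 15% missing it is nearly exact. Dosage coded by visit or crossed with time can move the estimate, but only to the extent that dose differs between arms, and that movement has a causal reading only without unmeasured need confounding.

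A reader might infer that the treatment effect itself is biased, or that the bias of a dose-adjusted estimate is known. Neither follows. The primary model contains no dosage term, and the figures in step 3 rest on assumed dose differences, correlations and need effects. The size in this trial is unknown.

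**What to change.** Amend section 3 as follows:

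1. As the check on section 2.8's expectation, report the between-arm difference in visits and in contact time with 95% confidence intervals, described as a post-randomisation result.
2. Remove dosage as an ordinary covariate and from the list of effect modifiers. If a dose-adjusted estimate is kept, regress the six-month score on group, baseline score, dose and baseline need, label it non-randomised, and state that it depends on no unmeasured need confounding.
3. Test age group and primary diagnosis as group × time × modifier.

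The cost is a few sentences. Contacts are already being recorded, the primary model and sample size stay as they are, and there is time, since "Data analysis will begin only after the follow-up stage". The downside is that no simple dose-adjusted estimate will be available and the exploratory results will be imprecise at n = 60: even an observed dose difference of zero would not exclude a true difference of about 0.5 SD.

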##### Inclusion criteria

2.2.1.1

Adults aged ≥18 years with diagnosed physical disabilities who are newly referred to and eligible for HCS, who are medically stable, and who are able to provide written consent.

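### Testing effect modification by age group rather than age in years gives up information in an exploratory analysis already limited by sample size

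*Protocol article*

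**What the plan says.** The Data analysis section lists three candidate effect modifiers: "interaction terms between group allocation and age group, primary diagnosis, and treatment dosage will be examined". Age is therefore to be used in groups, and no version with age in years is mentioned. The section is open about the status of this work: "Although the study is not powered for formal subgroup comparisons, exploratory sensitivity analyses will be performed to examine potential effect modification". It adds: "These analyses are exploratory in nature and will be interpreted cautiously given the limited sample size".

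Under Inclusion criteria the population is described as "Adults aged ≥18 years with diagnosed physical disabilities who are newly referred to and eligible for HCS", with no upper age limit. The article does not say how age is recorded. That it is held in years is a safe inference from an eligibility threshold in years, but it remains an inference.

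**The concern.** Using age group as the modifier is a choice the article makes, not a detail it leaves open. Banding treats everyone within a band as the same age and lets the treatment effect change only at the band edges. If the effect drifts steadily with age, the variation within bands carries information about that drift, and the banded model cannot use it. In a trial of 60 adults whose ages may span a wide range, that information is scarce, and interpreting the result cautiously does not bring it back. At stake is the precision of one exploratory interaction estimate: a real gradient is somewhat more likely to be missed, and its confidence interval is wider than it needs to be.

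**Working it through.** **The plan's own figure.** Sample size determination works "with a α level of 0.05 (two-tailed), a power of 0.80, and an effect size of 0.8 as reported" and states that "a minimum sample size of approximately 26 participants per group (a total of 52 participants) was determined". A two-sample t-test with d = 0.8 and two-sided 0.05 has power 0.807 at 26 per group and 0.791 at 25, so 26 is reproduced. With 60 recruited and 15% attrition, 60 × 0.85 = 51 completers. The article gives no figure for the age interaction, so the rest is illustration under stated assumptions.

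**Information kept by banding.** If the treatment effect is linear in age, the share of information on the slope that survives banding is the between-band variance of age divided by its total variance.

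- Normal age, median split: the half means are ±√(2/π) SD, so the share kept is 2/π = 0.637 and the loss is 36%. This is like analysing 51 × 0.637 ≈ 32 completers with continuous age.
- Normal age, equal thirds: the outer means are about ±1.091 SD, so the share kept is (2/3) × 1.091² ≈ 0.793 and the loss is 21%. This is like 51 × 0.793 ≈ 40 completers.
- Uniform age, k equal bands: the share kept is 1 − 1/k². Five bands keep 0.96, a loss of 4%.

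The loss under other assumed age shapes and banding schemes (left-skewed is a beta(4,2) shape):

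| Bands | Normal | Uniform | Left-skewed |
|---|---|---|---|
| Two, 50/50 | 36% | 25% | 33% |
| Two, 70/30 | 42% | 37% | 47% |
| Two, 80/20 | 51% | 52% | 60% |
| Three equal | 21% | 11% | 18% |
| Four equal | 14% | 6% | 11% |
| Five equal | 10% | 4% | 8% |

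**Effect on power.** Take residual SD 1, 1:1 allocation (variance of the group indicator 0.25) and age standardised to SD 1. The standard error of the interaction slope is √(1/(51 × 0.25)) = 0.28. Power is approximately Φ(b√e/0.28 − 1.96), where b is the gradient in SD of outcome per SD of age and e is the share of information kept.

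| Gradient b | Continuous age | Median split |
|---|---|---|
| 0.2 | 11% | 9% |
| 0.3 | 19% | 14% |
| 0.4 | 30% | 21% |
| 0.8 | 82% | 63% |

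At b = 0.4, for example, 0.4/0.28 − 1.96 ≈ −0.53 gives 30%. With 0.4 × √0.637 ≈ 0.319, the median split has 0.319/0.28 − 1.96 ≈ −0.82, which gives 21%. A noncentral F calculation agrees: at b = 0.4, 29% and 20%, with 18% for equal thirds (2 df); at b = 0.8, 80% and 61%, with 59% for equal thirds.

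**How steep these gradients are.** Between ages one SD below and one SD above the mean, the treatment effect changes by 2b. At b = 0.4 that is 0.8 SD, as large as the whole effect the trial is powered for. At b = 0.8 it is 1.6 SD, twice that effect. The last row is therefore not a realistic guide to what the change would buy.

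**The case against.** The strongest reply is that little turns on this. The section discloses the lack of power and labels the analyses exploratory, and no hypothesis or sample-size figure uses the age term. At gradients one could believe, the interaction is poorly estimated either way. All of that stands, and it fixes the weight of the point as minor. It does not make banding the better choice.

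A second reply is that continuous age has a cost of its own. In a mixed adult population with no upper age limit, a single linear term can miss a threshold or a non-monotone pattern that bands would show, and a linearity check on about 51 people is weak. This also stands, and the change should not be presented as free of any downside.

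Three stronger readings are tempting and are not supported:

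- A reader might infer that the cut-points are open to choice once the data are seen, or are arbitrary. The article says neither. Band definitions are commonly left to an analysis plan, which is not at hand, so their absence is no fault.
- A reader might take a loss of a fifth to a third as a property of this plan. It holds roughly for three or two equal bands of near-normal age, none of which the article states.
- A reader might take the fall from 82% to 63% power as typical. It needs the extreme gradient described in the working.

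**Conclusion.** The point holds as a minor, optional improvement. The article commits to age group as the modifier, and if effect modification is roughly linear in age this loses information in every scheme examined. The loss is about 36% for a median split and 21% for equal thirds of near-normal ages, within a range of about 4% to 60% depending on the bands and the age distribution. These are assumptions, since the article gives neither. The gain in power is modest: about 9 percentage points (30% against 21%) at 0.4 SD per SD of age with 51 completers, and less for shallower gradients. The conclusion rests on approximate linearity and on age being recorded in years. The stated sample size and the primary and secondary conclusions are unaffected.

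**What to change.** In the Data analysis section, replace age group with age in years, centred, in the interaction with allocation. Report the estimated treatment effect with its 95% confidence interval at two or three illustrative ages named in advance. Show a check of linearity alongside, and say that it has limited ability to detect departures at this sample size. Keep age bands for descriptive tables.

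The cost is a small wording change, with no new data (provided age is recorded in years) and no change to the sample size. The one statistical price is reliance on a linear term. The article says analysis starts only after follow-up, which is expected to end by 31 July 2026, so on those dates the change can be recorded before any outcome analysis.
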